## Abstract

**Background:**

Cardiovascular disease (CVD) is the leading cause of death globally, and accounted for nearly 31% of all deaths in Australia in 2011. The primary health care sector is at the frontline for addressing CVD, however, an evidence-to-practice gap exists in CVD risk assessment and management. General practice plays a key role in CVD risk assessment and management, but this sector cannot provide ongoing lifestyle change support in isolation. Community-based lifestyle modification services and programs provided outside the general practice setting have a key role in supporting and sustaining health behavior change. Fostering linkages between the health sector and community-based lifestyle services, and creating sustainable systems that support these sectors is important.

**Objective:**

The objective of the study Model for Prevention (MoFoP) is to take a case study approach to examine a CVD risk reduction intervention in primary health care, with the aim of identifying the key elements required for an effective and sustainable approach to coordinate CVD risk reduction across the health and community sectors. These elements will be used to consider a new systems-based model for the prevention of CVD that informs future practice.

**Methods:**

The MoFoP study will use a mixed methods approach, comprising two complementary research elements: (1) a case study, and (2) a pre/post quasi-experimental design. The case study will consider the organizations and systems involved in a CVD risk reduction intervention as a single case. The pre/post experimental design will be used for HeartLink, the intervention being tested, where a single cohort of patients between 45 and 74 years of age (or between 35 and 74 years of age if Aboriginal or Torres Strait Islander) considered to be at high risk for a CVD event will be recruited through general practice, provided with enhanced usual care and additional health behavior change support. A range of quantitative and qualitative data will be collected. This will include individual health and well being data collected at baseline and again at 12 months for HeartLink participants, and systems related data collected over the period of the intervention to inform the case study.

**Results:**

The intervention is currently underway, with results expected in late 2015.

**Conclusions:**

Gaining a better understanding of CVD prevention in primary health care requires a research approach that can capture and express its complexity. The MoFoP study aims to identify the key elements for effective CVD prevention across the health and community sectors, and to develop a model to better inform policy and practice in this key health priority area for Australia.

## Introduction

### Cardiovascular Disease in Australia

Cardiovascular disease (CVD) is the leading cause of death globally, and accounted for nearly 31% of all deaths in Australia in 2011 [1]. CVD accounted for the greatest spending at 12% ($7.6 billion) of all allocated health care expenditure in 2008-2009 [2]. Addressing lifestyle risk factors (eg, physical activity, diet, and smoking) can reduce the risk of premature mortality by 66% [3]. The use of a cardiovascular absolute risk (CVAR) approach to the primary prevention of CVD, rather than the traditional single risk factor focus, is now well established and is a recommended approach to practice in Australia [4]. Despite the evidence base and demonstrated cost effectiveness of a CVAR approach, application of this method for identification and management of CVD risk is not the usual practice in Australia [5].

### Cardiovascular Disease Prevention in Primary Health Care

Primary health care is at the frontline for the delivery of services that identify, prevent, and manage CVD risk. General practice plays a key role; however, this sector alone cannot provide the ongoing behavior change support that is often required for people at elevated CVD risk. Community-based lifestyle modification services and programs provided outside the general practice setting can have an important role in supporting and sustaining health behavior change. Fostering linkages between the health sector and community-based lifestyle services has been shown to improve population prevention outcomes [6].

The advent in 2011 of Medicare Locals, Australia’s primary health care organizations, is particularly relevant to efforts to improve CVD prevention. Given their role of operationalizing the government’s primary health care improvement program, the Medicare Locals are key agents in supporting the primary health care sector by undertaking chronic disease prevention and management activities [7]. The development of the general practice workforce via incentives to employ practice nurses and funding for the community sector to deliver community-based lifestyle modification programs is also significant [8,9]. These initiatives, along with the Medicare Locals, have the potential to increase the general practice and community sector capacity to support improved CVD prevention.

### The Chronic Care Model

To support the development of chronic disease prevention and management systems, and to improve practice and enhance the collaboration between sectors, a number of models and frameworks have been used. Such models can act to communicate a vision to different stakeholders, prompt dialogue between groups, and help to define goals and objectives for activities [10]. In the area of chronic disease prevention and management, specific models have been used successfully to inform and evaluate activities. The Chronic Care Model (CCM) has been central to chronic disease policy and practice globally since the late 1990s, and has been successful in driving quality improvement in chronic disease management [11]. Studies using the CCM as an implementation framework have consistently argued that system and patient level outcomes can be achieved by the implementation of the CCM, or even just some of its elements [12].

In 2001, Glasgow et al identified the potential for the CCM to be applied to the prevention of chronic disease [13]. They noted the many activities applicable to both chronic disease prevention and management, and identified that both require a proactive and system-oriented approach. The Expanded Chronic Care Model (ECCM) developed by Barr et al [14], combines the CCM with the action areas of the Ottawa Charter, a well known framework for health promotion [15]. Both the CCM and the ECCM have been identified as having the potential to inform improved CVD prevention practice [16,17]. However, the best model to improve practice in CVD prevention in primary health care is yet to be determined.

The Model for Prevention (MoFoP) study aims to build on the CCM and related models, identifying the key elements of a new systems-based model for the prevention of CVD that informs best practice.

### The Model for Prevention Study

The MoFoP study aims to investigate a whole-of-system approach to the prevention of CVD in the primary health care setting. The MoFoP study will examine the *HeartLink* CVD risk reduction intervention in primary health care. The study will identify key elements of improved CVD prevention practice across the health and community sectors.

The aims of the MoFoP study are to: (1) test the feasibility of the *HeartLink* pilot processes including organizational readiness and resource implications for each key stakeholder group with regards to the implementation of the intervention; (2) measure the efficacy of the *HeartLink* pilot in six general practices in the Australian Capital Territory (ACT), Australia; and (3) identify the key elements of an effective model for the prevention of CVD in primary health care, and critical success factors for implementation and sustainability.

A mix of interrelating theoretical and framing approaches governing different aspects of the study have guided the study. For example, the trans-theoretical model of behavior (stages of change) informs individual behavior change [18], the normalization process theory relates to the implementation of the intervention [19], with the expanded chronic care model and complex adaptive systems approach providing overarching frameworks [14,20].

## Methods

### Study Design

#### The Two Research Elements

The MoFoP study will use a mixed methods approach to evaluate the *HeartLink* pilot, comprising two complementary research elements: (1) a case study, and (2) a one-group pre/post quasi-experimental design acting as a pilot for a proposed larger cluster randomized trial. The study design was informed by the mixed design approach used by Provost et al [21].

#### Case Study

We will use an embedded single case study design as described by Yin [22]. Yin defines a case study as an empirical inquiry that, “investigates a contemporary phenomenon within its real-life context; when the boundaries between the phenomenon and context are not clearly evident, and in which multiple sources of evidence are used”, and where case study data is collected to test preidentified theoretical propositions. The study will consider the organizations and systems involved in the *HeartLink* intervention as a single case, with a number of aspects being examined as separate units of analysis within the case. Figure 1 illustrates this idea. This strategy will use quantitative and qualitative methods, and will consider a range of measures. The outcome of this descriptive case study will be a narrative of the case.

**Figure 1 figure1:**
[figure not shown]
Units of analysis forming the components of the Model for Prevention (MoFoP) study.

#### One-Group Pre/Post Quasi-Experimental Design

The second component, the *HeartLink* intervention, uses a preexperimental, one group pre/post test design. A single cohort of patients 45-74 years old (or 35-74 years old if Aboriginal and/or Torres Strait Islander) considered to be at high risk for a CVD event within the next five years will be recruited through general practices, and provided with enhanced usual care and additional health behavior change support. CVAR for each patient will be determined using the Australian adaption of the Framingham based CVD risk score, with high risk being defined as a CVAR > 15% over the next 5 years [4].

The design has been informed by interventions in Australia and the United Kingdom, which also aimed to achieve CVD risk reduction through enhanced risk identification and reduction programs in primary health care [23-25]. *HeartLink* will use the ECCM as a framework to create improved prevention pathways in the primary health care sector, including providers of lifestyle modification services and programs outside the traditional health sector.

### HeartLink Practice Recruitment

*HeartLink* is set in the ACT, Australia, and is a pilot intervention in six general practices, which have been selected to broadly represent of the socioeconomic and demographic population in the region.

The practices that are recruited will be required to meet a number of inclusion criteria, including: (1) agreement that the patient has no additional payment to make from participation in the first recall visit and the 12 month follow-up visit, (2) agreement to have at least one practice nurse on staff to support the intervention, and (3) have the PEN Computer Systems Pty (Sydney, Australia) Clinical Audit Tool software.

### HeartLink Patient Sampling Strategy and Sample Size

The patient sample size for the *HeartLink* intervention was determined by an examination of similar pilot studies [25]. However, resource constraints and the desire to minimize the burden on participating practices determined the final pilot sample size of 30 patients in each of the six practices, a sample of 180 in total. Due to the variability in practice population sizes, potential losses due to poor recall response, and failure to join or complete the intervention, which could be as high as 80% of the eligible registered patients in some practices (this is estimated from pilot work on practice data download and CVAR calculation), the aim is to recall as many patients with a CVAR > 15% as possible, within the six month recruitment period. A high dropout rate is expected due to the number of steps involved in moving from patient identification, to recall and recruitment, and finally to program participation and completion. This sample size should provide estimates of key parameters, such as possible effect size for the change in CVAR for patients, so that the optimal design of a full evaluation trial can be determined (see data analysis).

### HeartLink Participant Eligibility and Recruitment

Inclusion and exclusion criteria for *HeartLink* were established. Patients needed to be 45-74 years old (35-74 years old for Aboriginal and/or Torres Strait Islander people), have a CVAR >15% over the next five years, and an absence of established CVD, diabetes, or a previous cardiovascular event
to be included. Patients were excluded if they had not attended the general practice in the last two years, had a complex coexisting medical condition or impairment, were non-English speaking, or were excluded from the intervention by their general practitioner.

The patients participating in the intervention will be recruited through their usual general practice. Each of the pilot general practices uses a clinical software program to manage patient information and possesses a clinical audit tool. The clinical audit tool has a CVD risk calculator report function that generates a list of patients (from the clinical software records) meeting the CVAR inclusion criterion of associated risk level. The CVAR calculator uses age, gender, systolic blood pressure, smoking status, and serum lipids to calculate risk. A history of left ventricular hypertrophy and having diabetes are also identified.

An initial list of patients with a CVAR > 15% will be generated for each practice, and from this list random subsamples in batches of around 20 patients (the actual number depending on practice size and available resource) will be generated at scheduled intervals. As each sample is identified, the invitation letters will be posted (with up to two reminders) to invite participants to attend their practice for a “heart and stroke check”. Those attending the practice for the check will be offered participation in a health behavior change program if they are eligible. The scheduled sampling will occur over a six month period until the target sample size is achieved. Figure 2 shows the *HeartLink* participant pathway.

The University of Canberra’s Human Research Ethics Committee approved this study (Project number 11-141).

**Figure 2 figure2:**
[figure not shown]
HeartLink pilot participant pathway. CVAR: cardiovascular absolute risk, GP: general practitioner.

### HeartLink Intervention Description

#### Enhanced Usual Care in General Practice for Patients at High Risk of Cardiovascular Disease

The aims of the *HeartLink* pilot are to work with general practices to enhance care in relation to identification, recall, assessment, and management of patients at high risk of CVD. The intervention follows the evidence-based “5A’s” approach, with key steps integrated across the pilot design [26]. Upon recruitment, support will be provided to all of the participating general practices to audit their patient data, establish or improve data quality processes, and, where required, encourage processes to improve the levels of preventative activities such as measurement and recording of patient blood pressure. These actions are expected to maximize the patient numbers for recruitment, and will support the broader aims of the pilot to improve systems for the prevention and management of CVD in the pilot practices.

The PEN Computer Systems Pty Clinical Audit Tool CVD risk report will be used for the population of each practice, except those not attending the practice for more than two years, as it is likely that they are no longer patients of the practice or do not have a regular general practitioner (GP) at the practice. The patients identified as having a risk score of >15% on their most recently recorded clinical information will be sent a letter asking them to visit for a “heart and stroke” check [4]. The patients whose most recent cholesterol measures are greater than six months old will be sent a pathology request form along with their recall letter to encourage them to update their lipid levels before they attend their recall visit.

When patients arrive for their recall visit, they will have their CVAR recalculated by the practice nurse before a consultation with their GP.

As part of the recall visit to the general practice at baseline and 12 months, the CVD risk factor information required to calculate the absolute risk will be collected. The practice nurse in the clinical environment will measure the blood pressure, and the cholesterol level measurement (total and high-density lipoprotein cholesterol) will have been undertaken by a commercial pathology service provider upon referral from the GP prior to the visit. The smoking status, defined as smoker or nonsmoker (self-reported), will be recorded.

The GP consultation will comprise the usual care in relation to the management of the patient’s CVD risk profile, including making referrals to allied health professionals or medical specialists as required. GPs and practice nurses in participating practices will be offered professional development with regards to CVAR management guidelines, and will be provided with copies of the guidelines. After the GP consultation, the patient then returns to the practice nurse to consolidate the information provided by the GP. The patients will receive a brief intervention related to lifestyle modification and medication adherence, supported by Heart Foundation print material. The practice nurse consultation will be informed by the Health Change Australia (HCA) approach to health behavior change, and will aim to improve patient readiness for lifestyle change [27,28]. *HeartLink* uses the HCA approach across the intervention to provide patients with a consistent health behavior change paradigm, reinforced at each contact.

The eligible patients will then be offered participation in the health behavior change support program. If patients do not wish to progress to the program or are deemed by their GP to be ineligible, they will be given information on other health behavior change support options and offered ongoing usual care. The eligible patients who are initially not prepared to participate in the program will be provided with an opportunity to join the program at a later stage if they recontact their general practice within the recruitment timeframe of six months. The patients who are eligible and agree to participate in the health behavior change support program will be referred to the *HeartLink* Lifestyle Advisor linked to their practice.

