### Data Collection

#### Primary Health Outcome Measure

The primary health outcome measure for the study will be the change in the CVAR percentage score for the *HeartLink* intervention participants. A range of patient-reported health and well being outcomes will also be examined, including physical activity levels, fruit and vegetable intake, CVD medication adherence, health related quality of life, generalized self-efficacy, and intention to change key health behaviors related to CVD risk reduction.

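### Part of any fall in CVAR may be regression to the mean: patients enter on CVAR above 15%, and the one-group change in that score is called efficacy and used to plan the cluster trial

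*Protocol article*

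**What the plan says.** All references are to the protocol article.

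- **Selection.** One-Group Pre/Post Quasi-Experimental Design sets the cut-off: "high risk being defined as a CVAR > 15% over the next 5 years". HeartLink Participant Eligibility and Recruitment makes it an inclusion criterion. The Enhanced Usual Care section makes it the trigger for recall: "The patients identified as having a risk score of >15% on their most recently recorded clinical information will be sent a letter".
- **Second score before the program.** At the recall visit, "they will have their CVAR recalculated by the practice nurse before a consultation with their GP". The same section treats this visit as baseline and repeats the measurements at 12 months. A new lipid test is requested only when the last one is more than six months old.
- **Outcome.** "The primary health outcome measure for the study will be the change in the CVAR percentage score" (Primary Health Outcome Measure).
- **Design and aim.** The Two Research Elements describes "a one-group pre/post quasi-experimental design acting as a pilot for a proposed larger cluster randomized trial". The second aim is to "measure the efficacy of the *HeartLink* pilot in six general practices" (The Model for Prevention Study).
- **Use of the result.** The sample size section and Quantitative Data Analysis both say that the effect size will inform the design of the larger study.
- **Limitations.** Small scale, opt-in practices, a single city and imperfect standardization are listed. Regression to the mean is not named there or anywhere else in the article.

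**The concern.** The score uses systolic blood pressure and serum lipids, which vary on repeat measurement. People chosen because such a score is above a threshold include some whose value was high by chance on that occasion, and their next value tends to be lower without any treatment. When the selecting score is also the outcome and there is no concurrent control, a simple before-and-after comparison cannot separate that drift from a program effect.

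Two conclusions depend on this. One is the pilot's own statement about efficacy. The other is the effect size handed to the cluster trial: if it contains an artefact, the trial is planned too small.

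**Working it through.** **1. The plan's own figure.** 6 practices × 30 patients = 180, which reproduces. It was set by resources and practice burden. No SD, effect size or power is stated, so there is no power calculation to reproduce.

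**2. Inputs that must be assumed.** The article gives no distribution of CVAR, no repeat-measure reliability and no SD of change. Assumed here: practice mean/SD of 8/5 or 10/6 points (normal), reliability ρ from 0.7 to 0.9, and no true change. A second model used a log-normal CVAR (median 6 to 10%, log-SD 0.6 to 0.8) with ρ from 0.80 to 0.95.

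**3. Regression from the list score.** Expected fall = (1 − ρ) × SD × φ(c)/(1 − Φ(c)), with c = (15 − mean)/SD.

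For mean 8, SD 5, ρ = 0.8: c = 1.4, φ(c)/(1 − Φ(c)) = 0.1497/0.0808 = 1.85, so the fall is 0.2 × 5 × 1.85 = 1.85 points. Simulation gave 1.85. Over the assumed inputs the range is 0.8 to 2.8. This is the list-to-recall fall expected in attenders; it is not the planned outcome, because the article's baseline is the recall visit.

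**4. Regression from the recall-visit baseline to 12 months** (simulation, normal model, no true change):

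| Is >15% applied again at recall? | List and recall errors | Spurious fall (points) |
|---|---|---|
| No | independent | 0.0 |
| Yes | independent | 0.5 to 1.7 |
| No | correlated 0.71 | 0.6 to 2.0 |
| Yes | correlated 0.71 | 0.8 to 2.6 |

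The log-normal model gave 0.3 to 2.6 with the cut-off applied again and about 0 without it (independent errors). The correlation of 0.71 is illustrative. In the third row the fall is that correlation times the step 3 figure (0.71 × 2.78 = 1.97 at the top), so less sharing gives proportionally less bias.

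The re-application rule is not a detail. In the normal model with independent errors, only 44% to 75% of listed patients were still above 15% at recall.

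**5. Could an artefact pass as an effect?** Assume a change SD of 4, near the top of the 2.1 to 4.3 that noise alone produced in the re-selected cohort. With 180 pairs the SE is 4/√180 = 0.298. A pure artefact of 1.0 point is significant at two-sided 5% with probability Φ(1.0/0.298 − 1.96) = 0.92. For 0.5 point it is 0.39. With 90 pairs the figures are 0.66 and 0.22.

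**6. Effect on the later trial.** Per arm, before cluster inflation, n = 2(1.96 + 0.8416)² × 4²/δ². Suppose the true effect is 1.0 point.

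- Planned on 1.0: 252 per arm, power 80%.
- Planned on 1.5 (0.5 of artefact): 112 per arm, true power 46%.
- Planned on 2.0 (1.0 of artefact): 63 per arm, true power 29%.

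**The case against.** The strongest reply is that the protocol already re-measures. Baseline is the recall visit, and if everyone recalled is followed from there with fresh, independent measurements, regression has already happened by baseline and the bias is about zero. A reader might infer that the baseline is certainly truncated at 15%, so that a spurious fall is bound to be credited to HeartLink. The text does not go that far. Eligibility and Recruitment says the audit-tool list meets the CVAR criterion, and then offers the program after the check to those who are eligible, without saying whether the recalculated score must exceed 15%. The participant pathway figure, not available here, may settle it. Requiring the criterion at the visit is the plain reading, but it remains a reading.

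Further points that stand:

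- Every magnitude above is assumed. Age is an input to the score, so a year of ageing raises CVAR and offsets part of the fall. A net fall without any effect is not established.
- The list-to-recall change is an imperfect gauge. Records differ in age, data-quality work may correct them, reused lipids shrink the apparent regression, and attenders select themselves.
- The pilot status is open: the design is called preexperimental, and the limitations section assigns the question of effectiveness to a later trial with control practices.
- Because invitations go to "from this list random subsamples in batches of around 20 patients", a reader might take listed patients who were never drawn as a ready concurrent control. That does not work. The plan is to recall as many high-risk patients as possible, so few may remain. Those who do are exposed to the practice-level training, audit and promotion, and without re-measurement their recorded blood pressure and lipids would not regress.

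What the reply does not answer is the combination the article states: selection on the outcome, an uncontrolled comparison, the word efficacy, and an effect size carried forward. Pilot status would excuse a descriptive aim. It does not make the effect estimate safe for planning. Nor does the point depend on detail that an article leaves to an analysis plan, since aim, selection rule, outcome and limitations are all given here.

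**Conclusion.** The concern holds in conditional form. Part of any fall in CVAR may be regression to the mean. It is expected if the 15% cut-off is also required of the recall-visit score, or if list and recall scores share data such as lipids under six months old. It is about zero if neither applies.

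With the recall visit as baseline, the artefact is roughly 0.3 to 2.6 points across the assumed distributions, reliabilities and error correlation, before a partial offset from ageing that the documents do not allow to be sized. An artefact of about 1 point, if it occurred, would usually reach significance at 180 pairs and could leave the cluster trial badly underpowered. The wording of the second aim and the unadjusted use of the effect size are not supportable as written, whichever branch applies, because a one-group change cannot measure efficacy.

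**What to change.** 1. Keep the recall-visit CVAR as baseline, and state whether a value above 15% is required of it.
2. Retain the list score, and report the list-to-recall change in all attenders, including those recalculated at or below 15%.
3. Report the 12-month change unadjusted and, as a sensitivity analysis, net of the regression to the mean expected from step 2. Say that the correction is approximate because of record age, reused lipids and self-selected attenders.
4. Reword the second aim from measuring efficacy to describing the change in CVAR.
5. Name regression to the mean and the lack of a concurrent control in the limitations.
6. Do not size the cluster trial on the unadjusted pre/post effect.

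These are changes to analysis and wording, so they remain possible although the Results section says the intervention is complete. Step 2 depends on the list scores having been kept, which the article does not say. The cost is a smaller and less certain headline change.
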